## 1. Study Summary

|                                                   |                                                                                                                                                                                 |
|---------------------------------------------------|---------------------------------------------------------------------------------------------------------------------------------------------------------------------------------|
| Study Title                                | A mixed methods approach to examining decisional needs and contextual factors influencing fertility status assessment outcomes among young female survivors of childhood cancer |
| Study Design                               | Cross-sectional survey                                                                                                                                                          |
| Primary Objective                          | Explore the perceived reproductive health needs of emerging adult female cancer survivors                                                                                       |
| Secondary Objective(s)                     | Identify decisional and contextual factors that influence pursuit of fertility status assessment                                                                                |
| Research Intervention(s)/Interactions      | Cross-sectional survey, semi-structured interview                                                                                                                               |
| Study Population                           | Female survivors of childhood cancer, aged 18.00-29.99 years with a history of gonadotoxic treatment                                                                            |
| Sample Size                                | 325                                                                                                                                                                             |
| Study Duration for individual participants | Survey completion is estimated 20 minutes; semi-structured interviews estimated 45 minutes                                                                                      |

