### **Data to be collected**

**Medical Record Data:** **Clinical Characteristics**, including cancer diagnosis, date of diagnosis, number of cancer survivor clinical encounters, hormonal laboratory assessments, prior hormone treatment, gonadotoxic therapeutic exposures [alkylating and heavy metal chemotherapy, gonadotoxic radiation], surgeries, history of hematopoietic cell transplant, and date of cancer treatment completion will be abstracted from participant's medical records by the site CRC using an adapted version of the COG Summary of Cancer Treatment Template.

[figure not shown]

**Quantitative Survey Data:** Participants will be invited to complete a web-based REDCap survey assessing sociodemographic and developmental factors, reproductive factors (knowledge, concerns, behaviors, and health needs), psychological factors, and history of FSA. The survey instrument is included with this protocol.

**Sociodemographic factors** include gender identity, race/ethnicity, religion, education level, household income, insurance and relationship status, and items are consistent with national surveys of young adults. **Developmental factors** will be assessed through the lens of emerging adulthood using The Markers of Adulthood (MoA) scale, which characterizes the attainment of behavioral milestones among emerging adults, and the IDEA-8 characterizes a self-perceived state of transition (e.g., feeling in-between); both scales have been used in large multi-site studies with emerging adults across diverse populations.

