**Reproductive knowledge** will be assessed using an overall score of correct answers (0-12) to items regarding cancer and fertility preservation. Gaps in knowledge will be assessed through self-reported knowledge level (item response options include none, a little, a lot) regarding fertility after cancer (e.g., impact of cancer treatment on fertility, knowledge of infertility testing and treatment). Survivors will also report their perceived risk for infertility (none, low, moderate, high) and how they perceive their risk for infertility compared with peers who have not had cancer. The modified **Reproductive Concerns Scale (mRCS)** consists of 7 items with 3 subscales measuring participant's fertility-related concerns, illness concerns related to pregnancy/parenthood, and information-seeking regarding reproductive health. The mRCS has been validated among adolescent and young adult survivors of childhood cancer. **Fertility-related distress** will be assessed using three domains of the Fertility Problem Inventory (FPI), a 27-item multidimensional scale measuring infertility stress, impact on social dimensions, and importance of parenthood and the Couple's Relationship Concern subscale from the Reproductive Concerns After Cancer scale; higher scores indicate increased distress. **Reproductive health behaviors** will include pregnancy and birth history, contraceptive history and current use, and sexual behaviors. **Reproductive health needs** will be assessed through items identifying unmet educational needs, desire for contraceptive counseling, and interest in FSA.

Psychological factors will also be assessed. **Decisional conflict** will be measured using the Decisional Conflict Scale, which measures four dimensions of decision making: information, values, support, and uncertainty; each subscale is scored 0-100 with higher scores indicating greater decisional conflict. The effective decision subscale will be used to measure **decisional satisfaction** among participants who have received an FSA; scores range from 0-100 with lower scores representing a good decision.

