## **10. Inclusion and Exclusion Criteria**

The population of interest for this study is female survivors of childhood cancer, 18 through 29 years of age.

Inclusion Criteria:

- (1) 18.00 to 29.99 years of age
- (2) diagnosis of cancer < 21.00 years of age
- (3) female sex
- (4) received gonadotoxic cancer treatment (e.g., alkylating chemotherapy agents, heavy metal chemotherapy, radiation including the gonads, cranial radiation  $\geq$  30 Gy, or hematopoietic cell transplant)
- (5) >1 year from completion of cancer treatment

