**Aim 1.3:** To assess associations between model parameters describing sociodemographic, clinical, reproductive health needs and decisional conflict (covariates) and receipt of an FSA (outcome), we will employ bivariable and multivariable binary logistic regression models. For all logistic regression models, model parameters for sociodemographic, clinical, reproductive health needs and decisional conflict will be treated as fixed effects and study sites will be evaluated as random effects, where appropriate, to account for potential differences in outcome variability between the study locations (i.e., clustering); moreover, fit statistics will be gauged (i.e., AIC, BIC, log-likelihood) for all regressions and appropriate assumptions will be checked, such as linearity in covariates and normality of residuals. Final multivariable results will be guided by the bivariable associations and determined using backward selection procedures, as well as any relevant clinician input. Estimates from these models will be presented as odds ratios for receipt of an FSA with 95% confidence intervals and p-values.

**Power Analysis:** The primary endpoint for this study will be receipt of an FSA. Based on insights from the literature, and our own clinical experiences, we anticipate 20% (n=65) of the sample will have received an FSA and 260 respondents will have not. These sample sizes, which will be obtained by sampling 4 study sites, achieve 80% statistical power to detect an odds ratio of 2.4 for discrete exposures. This odds ratio corresponds to 70.4% of respondents in the FSA group having the exposure, versus 50% of respondents in the non-FSA group having the exposure (i.e., a percent difference of 20.4%). Power was calculated in PASS v.14.0.8 (Kaysville, UT), with a two-sided un-pooled Z-test, an intra-cluster correlation (ICC) of 0.01, and a statistical significance level of 0.05.

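### Because entry requires gonadotoxic treatment, bivariable odds ratios for single exposures in Aim 1.3 compare one such treatment with the others, and letting them guide the final model can drop a real clinical factor

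*Protocol*

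**What the plan says.** Four statements in the protocol combine.

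- **Entry.** Section 1 defines the population as "Female survivors of childhood cancer, aged 18.00-29.99 years with a history of gonadotoxic treatment". Section 10, inclusion criterion 4, requires that the woman "received gonadotoxic cancer treatment (e.g., alkylating chemotherapy agents, heavy metal chemotherapy, radiation including the gonads", and goes on to list cranial radiation above a threshold and transplant. No participant is free of all qualifying exposures.
- **Data.** Section 6 (Data to be collected) lists among the clinical characteristics "gonadotoxic therapeutic exposures [alkylating and heavy metal chemotherapy, gonadotoxic radiation], surgeries, history of hematopoietic cell transplant".
- **Model.** Section 19, Aim 1.3, studies "associations between model parameters describing sociodemographic, clinical, reproductive health needs and decisional conflict (covariates) and receipt of an FSA (outcome") and states that "we will employ bivariable and multivariable binary logistic regression models".
- **Selection.** The same paragraph says: "Final multivariable results will be guided by the bivariable associations and determined using backward selection procedures", with clinician input as a further guide. Aim 3 repeats this rule.

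Section 19 names the covariates by class only. It does not list single exposures, fix their coding or reference group, or say whether they are entered together.

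**The concern.** A woman without exposure A is in the study only because she had B, C or D. The group without A is therefore richer in the other exposures than the group with A, even if the treatments were unrelated among all survivors. If B, C or D is related to FSA, the unadjusted comparison for A carries their effect with the sign reversed.

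Aim 1.3 is meant to identify clinical factors related to FSA and to inform an intervention. An unadjusted ratio pulled toward or below 1 matters little as a description. It matters more as a filter, because a real exposure that looks weak on its own may never reach the model in which its association would be visible.

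**Working it through.** **1. The plan's own figure.** Section 19 expects that "we anticipate 20% (n=65) of the sample will have received an FSA and 260 respondents will have not", and gives 80% power for an odds ratio of 2.4 (70.4% v 50% exposed), un-pooled Z-test, ICC 0.01, 4 sites.
- Design effects 1 + (m − 1) × 0.01, with m = 65/4 = 16.25 and 260/4 = 65: 1.1525 and 1.64.
- Effective sizes 65/1.1525 = 56.4 and 260/1.64 = 158.5.
- SE = √(0.704 × 0.296/56.4 + 0.25/158.5) = 0.0726.
- Power = Φ(0.204/0.0726 − 1.96) = 80.2%.

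The figure reproduces and the present point does not touch it. I take 2.4 from it as the yardstick.

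**2. Assumptions.** The protocol gives no exposure frequencies and no effects of single exposures. Those below are assumed, with exposures independent before the entry rule unless stated.

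**3. An exposure with no effect.** Take alkylator 60%, radiation 25%, other 25%, and FSA depending on radiation only (35% v 15%).
- The entry rule removes 0.40 × 0.75 × 0.75 = 22.5%.
- With alkylator, 25% have radiation: P(FSA) = 0.25 × 0.35 + 0.75 × 0.15 = 0.200.
- Without alkylator, radiation frequency is 0.25/(1 − 0.75 × 0.75) = 57.1%: P(FSA) = 0.571 × 0.35 + 0.429 × 0.15 = 0.264.
- Bivariable odds ratio = (0.200/0.800)/(0.264/0.736) = 0.70; the true value is 1.

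Other assumed sets, with FSA at 20% among eligible women, for the exposure with a true odds ratio of 1:

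| Exposure frequencies | Others related to FSA | Bivariable odds ratio |
|---|---|---|
| Two exposures (50/20, 50/30, 70/20%) | one, 2.4 | 0.52–0.57 |
| 50/30% | one, 1.5 | 0.76 |
| 60/20/20/10% | one / two / three, 2.4 | 0.87 / 0.70 / 0.59 |
| 60/20/20/10% | three, 1.5 | 0.77 |
| 80/30/30/20% | two / three, 2.4 | 0.77 / 0.69 |
| 60/20/20/10% | none | 1.00 |

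**4. A real exposure.** Four exposures at 60/20/20/10%, each with odds ratio 2.4.
- Removed by the entry rule: 0.4 × 0.8 × 0.8 × 0.9 = 23.0%.
- For the commonest, P(FSA) is 0.211 with and 0.162 without: (0.211/0.789)/(0.162/0.838) = 1.38.
- The other three show 1.78 to 1.80.
- Without the entry rule all four would show 2.25 to 2.29.

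**5. Effect of the selection rule.** Samples of 325 under the step 4 setting, with backward elimination at 0.05. The protocol names no screening threshold, so two are assumed. Result for the commonest exposure:

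| Procedure | In final model, or significant |
|---|---|
| Screen p < 0.05, then backward elimination | 13% |
| Screen p < 0.20, then backward elimination | 34% |
| All four entered together | 69% |

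Repeat runs of 2,000 to 3,000 samples, with Wald or likelihood-ratio tests, gave 13–16%, 32–34% and 65–68%. The same runs (Wald) without the entry rule gave 76%, 81% and 81%, so the loss comes from combining the entry rule with screening.

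**6. The opposite error.** In the step 3 setting the exposure with no effect is significantly protective in 22–25% of bivariable fits, but in only 2.2–3.3% of final models (nominal 2.5%). With three other exposures at 2.4 (60/20/20/10%), the figures are 35–38% and about 4–7%.

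**7. Correlated treatments.** In the step 3 setting, with a pre-selection alkylator–radiation odds ratio of 2, 3, 4 or 6, the bivariable ratio becomes 0.83, 0.93, 1.00 or 1.11.

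**The case against.** The strongest case against has five parts.

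- **Separate exposure terms are inferred.** This stands. Section 19 says only 'clinical', and coding may be settled in an analysis plan not shown. The point is therefore conditional on separate terms. The selection rule, however, is stated in the protocol itself.
- **There is a reference group.** A reader might infer that these odds ratios have no unexposed comparator. That goes too far. Each single exposure has women without it; only a group free of all exposures is missing, and that is by design.
- **The ratio is a valid description.** Aim 1.3 asks about associations within eligible survivors and claims no causal effect. This stands for a reported unadjusted ratio, provided it is read as a contrast with other gonadotoxic treatment. It does not answer the use of that ratio to decide which exposures enter the joint model.
- **Backward elimination corrects the artefact.** For a false protective term it largely does (step 6). It cannot restore an exposure that was screened out beforehand (step 5). Clinician input allows an exposure to be kept but does not ensure it.
- **Size and direction rest on assumptions.** This stands. Without joint exposure frequencies the distortion cannot be sized for this cohort, and strong positive correlation removes or reverses it.

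Also, surgery is abstracted but is not among the examples in criterion 4. Since those are only examples, and the Background counts surgery affecting the gonads as gonadotoxic, little turns on this.

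**Conclusion.** The point holds in conditional form. If the abstracted exposures enter Aim 1.3 separately, if at least one other exposure is related to FSA, and if treatments are not strongly positively correlated, the bivariable odds ratios are biased downward as measures of each exposure's own association. The size is about 0.5 to 0.9 for an exposure with no effect, and about 1.4 in place of 2.4 for the commonest of four. The main harm is loss of a real factor: kept in roughly 13% to 34% of simulated samples, against about two-thirds when all exposures are entered together.

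Two stronger readings are not supported. One is that the final model will commonly report a spurious protective exposure; the simulated rates stay near nominal or a few points above it. The other is that Aim 1.1 is deficient because perceived infertility risk is not graded against a treatment-based level. The protocol does not undertake to grade it, so that cross-tabulation is optional. The matter is worth correcting, but it does not invalidate Aim 1.3.

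**What to change.** In Section 19, Aim 1.3, state that:

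1. the qualifying treatment exposures are not screened on bivariable results;
2. they enter the multivariable model together and stay as one block (alkylating agents, heavy metals, gonadal radiation, cranial radiation, transplant), or are replaced by one ordered treatment-based risk level defined before analysis;
3. any unadjusted exposure odds ratio is labelled 'versus other gonadotoxic treatment'.

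Aim 3 repeats the selection rule, so the same wording should be considered there.

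The change is to wording, using exposures the protocol already plans to abstract. The cost is 4 to 5 degrees of freedom for the block, or 1 for the ordered level, against about 65 events shared with the other covariates. Five terms alone leave 65/5 = 13 events per term, so the ordered level is the cheaper choice if the remaining covariate list is long.

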## **7. Procedures – Long-Term Follow Up**

There are no long-term follow-up procedures.

## **8. Sharing of Results with Participants**

Study results will not be shared with participants or others, beyond scholarly dissemination of de-identified data through presentations and publications.

## **9. Study Timelines**

The estimated time for participants to complete the quantitative survey is 15-20 minutes; for participants who complete a qualitative interview, the estimated time is 45 minutes. We anticipate active study recruitment and data collection to be complete within 3 years.

## **10. Inclusion and Exclusion Criteria**

The population of interest for this study is female survivors of childhood cancer, 18 through 29 years of age.

Inclusion Criteria:

- (1) 18.00 to 29.99 years of age
- (2) diagnosis of cancer < 21.00 years of age
- (3) female sex
- (4) received gonadotoxic cancer treatment (e.g., alkylating chemotherapy agents, heavy metal chemotherapy, radiation including the gonads, cranial radiation  $\geq$  30 Gy, or hematopoietic cell transplant)
- (5) >1 year from completion of cancer treatment

**Exclusion Criteria:**

- (1) cognitive dysfunction, such that they would be unable to complete the survey
- (2) bilateral oophorectomy

## **11. Population**

The purpose of this study is to explore reproductive health and identify factors related to receipt of a fertility status assessment among female young adult cancer survivors. This study will enroll 325 female cancer survivors aged 18.00 through 29.99 years.

Pregnant women will not be excluded from participating in this research. Adults unable to consent, those with cognitive dysfunction, or individuals with impaired decision-making capacity will be excluded as they are unable to complete the study measures. Individuals who speak English or Spanish will be included in the quantitative survey aim of this study, which will be available in English and Spanish; only English-speaking individuals will be eligible to participate in the qualitative interviews.

## **12. Vulnerable Populations**

It is possible that some participants may be pregnant. We do not anticipate any additional risks from completing the survey or qualitative interview for participants who are pregnant. Strategies to ensure privacy, confidentiality, and reduce discomfort will be the same as for participants who are not pregnant.

Children will not be enrolled in this study. The health needs and decisional factors related to fertility assessment are influenced by age and development, therefore this study will be limited to focus on the unique developmental period of emerging adulthood. The minimum age limit (18.00 years) was chosen to include participants who are legally able to make independent medical decisions, such as pursuing a fertility status assessment.

## **13. Local Number of Participants**

The study will recruit 325 participants study-wide, with 100 participants enrolled locally at the Children's Healthcare of Atlanta/Emory University site. Participant eligibility will be confirmed prior to recruitment.

The purpose of this study is to explore reproductive health and decisional factors regarding fertility status assessment. The sense of urgency and factors that influence the decision to pursue a fertility status assessment are different for females and males,

therefore our planned enrollment includes 100% female participants. Transgender men will also be eligible for this study; gender identity will be self-reported as part of the survey data collection.

Participants of any race and ethnicity will be recruited for this study. Estimates of race and ethnicity enrollments are derived from site-specific databases that were used to estimate demographics of survivors who would meet the eligibility criteria for this study. The race and ethnicity of survivors vary across sites and are related to the demographic characteristics of the geographical region. Overall, across all sites, we anticipate 76.9% of participants will be white, 12.6% Black, 6.4% more than one race, 2.2% Asian, 1.2% American Indian/Alaska Native, 0.6% Native Hawaiian or other Pacific Islander. We estimate that 13.1% of white participants will be Hispanic and 2.4% of Black participants will be Hispanic. These estimates align with previously published population-based studies of survivors of childhood cancer. The study survey will be available in Spanish for completion on REDCap or via paper and pen.

#### **14. Recruitment Methods**

Recruitment procedures are based on strategies that have been successful with our research team in the past. The PI and research coordinator at each site will use site-specific databases, cancer registry data, or similar methods to identify patients who meet eligibility criteria (i.e., female sex, aged 18 through 29 years, history of cancer diagnosis <21 years of age, > 1 year from completion of cancer treatment, history of gonadotoxic treatment exposures). This approach has already been established and utilized at each site in order to provide details on estimated eligible participants. Once the list of potentially eligible patients is finalized, the list will be stratified by age group (18.00-24.99 and 25.00-29.99). Then each site will randomize their list, using excel or similar software, to begin consecutive recruitment. This approach will contribute to a more representative study sample. Site study teams will examine the medical records for patients prior to recruitment to verify eligibility.

The site research coordinator will recruit patients using various methods, depending on institutional approvals which include:

**Email/Epic MyChart.** An email/MyChart invitation including a link to the REDCap survey is the primary and preferred method of recruitment. The email will explain the purpose of the study, briefly outline the study procedures, and include site-specific contact information; there will also be instructions for patients to indicate if they decline participation and do not wish to be contacted further. Patients who are interested will click on the survey link. Participants will complete the REDCap survey (estimated time 15-20 minutes) and following completion the participant will be asked to provide contact information to receive the study gift card. A reminder email(s)/My Chart message can be sent for patients who do not respond.

**Phone Call:** For patients who do not complete the survey after receiving reminder emails/My Chart message, patients for whom email addresses are not available, and

sites who are unable to use email recruitment, will contact patients by phone. The site research coordinator will describe the purpose of the study and patients who are interested will be emailed a link to the REDCap survey or will be provided with a web address to access the survey. Patients who are unable or choose not to complete the survey online will be mailed a paper copy, with a self-addressed stamped envelope to return to the coordinating site. The study research coordinator will enter participant responses from paper surveys into the REDCap database.

Mail: Sites may recruit participants by mailing a letter describing the study and inviting participation.

In-person: Finally, if eligible patients have scheduled clinical visits within the oncology center, the research coordinator may recruit patients during the clinical encounter.

Recruitment methods will be tracked by the site research coordinators. Recruitment approaches may vary across sites to align with institutional processes. Patients may be contacted up to 5 times total for recruitment, which may be a combination of email/My Chart, phone call, or letter.

